|                                                                                                                                                                                                                                                                                                                                                              |                                                                                                                                                                                                                                                                                                                                                                                                                                           |
|--------------------------------------------------------------------------------------------------------------------------------------------------------------------------------------------------------------------------------------------------------------------------------------------------------------------------------------------------------------|-------------------------------------------------------------------------------------------------------------------------------------------------------------------------------------------------------------------------------------------------------------------------------------------------------------------------------------------------------------------------------------------------------------------------------------------|
| Dyspnea ≥ grade 2
Hypoxia ≥ grade 2
Pneumonitis/pulmonary infiltrates ≥ grade 2
Pulmonary fibrosis ≥ grade 2
Cough ≥ grade 3                                                                                                                                                                                  | Hold all therapy until interstitial lung disease is ruled out. 
 
• If non-infectious interstitial lung disease is confirmed, oxaliplatin must be discontinued.
 
• If non-infectious interstitial disease is ruled out and infection (if any) has resolved, patients with persistent Grade 2 dyspnea or hypoxia can resume treatment at the discretion of the investigator.
 
 |

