**8.2.3 Treatment management for patients receiving mFOLFIRINOX**

mFOLFIRINOX dose modifications for patients treated with mFOLFIRINOX are detailed in Table 8.2.3.2. Dose modifications are based on the dose level changes outlined in Table 8.2.3.1.

Additionally, the following dose modification instructions must be followed:

All doses must be based on the AE requiring the greatest modification.

Any chemotherapy doses that have been reduced may not be escalated.

- If  $\geq$  grade 2 toxicity occurs **during the 46-48 hour infusion of 5-FU**, discontinue the infusion and refer to Table 8.2.3.2 for dose modifications for the next cycle of mFOLFIRINOX.
- The leucovorin dose remains 400 mg/m^2 regardless of changes in the 5-FU, oxaliplatin, and irinotecan doses. If 5-FU is held, leucovorin should also be held.
- If oxaliplatin is discontinued, treatment should continue with 5-FU, leucovorin, and irinotecan.
- If irinotecan is discontinued, treatment should continue with 5-FU, leucovorin, and oxaliplatin.
- If 5-FU and leucovorin are discontinued, treatment should continue with irinotecan and oxaliplatin.

Table 8.2.3.1: Dose levels for mFOLFIRINOX

|                                                                                                                                                                              | Dose Level 0
Starting Dose
(mg/m  ) | Dose Level -1
(mg/m  ) | Dose Level -2
(mg/m  ) | Dose Level -3 |
|------------------------------------------------------------------------------------------------------------------------------------------------------------------------------|---------------------------------------------------------------------|----------------------------------------------|----------------------------------------------|----------------------|
| Oxaliplatin                                                                                                                                                           | 85                                                                  | 65                                           | 50                                           | Discontinue          |

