| Respiratory, thoracic and mediastinal disorders                                                                                                                                                                                                                                                                                                                                                                                                                         |                                                                                                                                                                                                                                                                                                                                                                                                                                        |                                                                    |
| Dyspnea ≥ grade 2
Hypoxia ≥ grade 2
Pneumonitis/pulmonary infiltrates ≥ grade 2
Pulmonary fibrosis ≥ grade 2
Cough ≥ grade 3                                                                                                                                                                                                                                                                                                                                | Hold all therapy until interstitial lung disease is ruled out. 

• If non-infectious interstitial lung disease is confirmed, oxaliplatin must be discontinued.

• If non-infectious interstitial disease is ruled out and infection (if any) has resolved, patients with persistent Grade 2 dyspnea or hypoxia can resume treatment at the discretion of the investigator.

 |                                                                    |

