- Mild-moderate diarrhea has been seen -- usually of short duration. Treat accordingly. See Section 8.1 for ancillary treatment.
- Respiratory problems (i.e., pulmonary fibrosis, cough, dyspnea, rales, pulmonary infiltrates, hypoxia, air hunger and tachypnea) have been observed in patients administered oxaliplatin. In rare cases, death has occurred due to pulmonary fibrosis. Please monitor and instruct the patient to report any respiratory difficulties and hold oxaliplatin until interstitial lung disease is ruled out for cases of Grade  $\geq 3$ . If patient is experiencing shortness of breath, a chest x-ray and assessment of oxygenation via either finger oximetry or arterial blood gas evaluation are required to confirm the absence or presence of pulmonary infiltrates and/or hypoxia (treat accordingly: no intervention, steroids, diuretics, oxygen, or assisted ventilation).
- Venous-occlusive disease (VOD) is a rare but serious complication that has been reported in patients receiving oxaliplatin in combination with 5-FU. This condition can lead to hepatomegaly, splenomegaly, portal hypertension and/or esophageal varices. Instruct patients to report any jaundice, ascites, or hematemesis to the MD immediately as these could be a sign of VOD or other serious condition.
- Acute vein irritation can occur with infusion. Apply heat to arm of infusion if you are using a peripheral line. However, extravasation of drug can cause severe pain, redness, soreness, and exfoliation of the skin in the affected area with loss of affected vein for a long period. If a patient has a problem with pain or sclerosis when chemotherapy is given by a peripheral line, then placement of a central line should be considered.
- Hemolytic Uremic Syndrome (HUS) may result in kidney damage. Oxaliplatin is to be discontinued in cases where hematocrit is  $<25\%$ , thrombocytopenia  $<100,000$ , and creatinine  $\geq 1.6$  mg/dL.
- Patients may experience sleep disturbances, specifically insomnia. Encourage good sleep hygiene, and instruct patient to report any problems with sleep to the MD, to assess for the potential use of sleeping aids.
- Cold-induced transient visual abnormalities can be experienced by patients while receiving oxaliplatin, although the relationship to oxaliplatin has not been completely determined. Instruct patient to report any problems with vision to the MD.

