**Rare known potential toxicities, <1% (Limited to important or life-threatening):**

ALT increased, amylase increased, anaphylactoid reaction, anaphylaxis, angina, arterial thrombosis, bleeding, Bradycardia, cardiac arrest, cerebral infarct, cerebrovascular accident, circulatory failure, colitis, deep thrombophlebitis, dysrhythmia, embolus, gastrointestinal bleeding, gastrointestinal obstruction, hepatomegaly, hiccups, hyperglycemia, hypersensitivity, hyponatremia, ileus, interstitial lung disease, intestinal perforation, ischemic colitis, lipase increased, lymphocytopenia, megacolon, MI, muscle cramps, myocardial ischemia, pancreatitis, paresthesia, peripheral vascular disorder, pulmonary embolus, pulmonary toxicity (dyspnea, fever, reticulonodular infiltrates on chest x-ray), renal failure (acute), renal impairment, syncope, thrombophlebitis, thrombosis, typhlitis, ulceration, ulcerative colitis, vertigo

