***Nursing Guidelines***

- Cholinergic symptoms of lacrimation, nasal congestion, diaphoresis, flushing, ABD cramping, and diarrhea can occur at the beginning, during, or immediately after the irinotecan infusion. It is suggested that the patient remain in the treatment area for a minimum of one hour following the completion of the **very first** irinotecan infusion.
- Patient education is extremely important. Impress on the patient the importance of compliance with treatment of diarrhea management. Stress the need for prompt recognition and early intervention. Motivate the patient to report any complications immediately. The cholera-like syndrome can be unresponsive to conventional antidiarrheals and can result in severe dehydration.
- Ondanestron and diphenhydramine should provide good relief from the nausea/vomiting/cramping. Avoid prochlorperazine on the day of treatment due to its association with akathisia (motor restlessness). Prochlorperazine may be taken between treatments.
- Advise avoidance of excess caffeine, a GI stimulant. Avoid magnesium-based antacids such as Mylanta, Maalox, Rolaids, MOM, Mag-Ox 400, and Tylenol with antacid.
- The pulmonary toxicity seen is usually manifested by dyspnea beginning 42-175 days after treatment and occurs at a cumulative dose ranging from 400-1000 mg/m (median 750). Instruct patient to report any cough or SOB.
- Patients are at risk for developing eosinophilia and will improve on steroid therapy.
- Hepatic enzyme elevations have been transient and did not require intervention.

- Monitor CBC closely. Leukopenia occurs primarily as neutropenia but can be severe and dose limiting. The simultaneous occurrence of grade 4 diarrhea and grade 4 neutropenia is rare but may render the patient more susceptible to polymicrobial sepsis and potentially death.
- Advise patients of probable hair loss.

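### In the mFOLFIRINOX arm the protocol gives conflicting instructions on irinotecan after confirmed interstitial lung disease, and Sections 8.2 and 10.2 differ on when, and for which drugs, treatment is held for respiratory events

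*Combined protocol and SAP*

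**What the plan says.** **Confirmed ILD, triplet arm.** The respiratory row in the continued part of Table 8.2.3.2 is triggered by events such as "Dyspnea ≥ grade 2". It holds all therapy until ILD has been excluded. If ILD is found, it says: "If non-infectious interstitial lung disease is confirmed, oxaliplatin must be discontinued". It does not mention irinotecan. Its only clause on resuming treatment concerns patients in whom ILD has been excluded.

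The bullets at the start of Section 8.2.3 are introduced as instructions that must be followed. One of them reads: "If oxaliplatin is discontinued, treatment should continue with 5-FU, leucovorin, and irinotecan". It makes no exception by reason for stopping oxaliplatin.

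**Irinotecan and the lung.** Section 10.6 includes ILD in its list of rare (<1%) known potential toxicities of irinotecan: "ileus, interstitial lung disease, intestinal perforation". The nursing guidelines in the same section add: "The pulmonary toxicity seen is usually manifested by dyspnea beginning 42-175 days after treatment", with a cumulative dose of 400-1000 and a median of 750.

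**When to hold.** Table 8.2.1.3, to which the mFOLFOX6, CAPOX and mFOLFIRINOX sections all refer for oxaliplatin-specific toxicities, has the same trigger terms and also holds all therapy "until interstitial lung disease is ruled out". The nursing guidelines in Section 10.2 instead tell staff to "hold oxaliplatin until interstitial lung disease is ruled out for cases of Grade" 3 or higher.

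**The concern.** A site managing a triplet patient with confirmed ILD needs to know what happens to each drug. The row settles oxaliplatin only. For irinotecan, which the protocol itself associates with ILD, the site finds a hold whose release condition has not been met and a general bullet that says to carry on. Two sites could follow the text in good faith and act differently.

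The second difference concerns the start of the process. Staff working from Section 8.2 hold every drug at grade 2 dyspnea. Staff working from Section 10.2 have a hold instruction only from grade 3, and only for oxaliplatin. What is at stake is participant safety and uniform conduct in a serious, uncommon event, where site staff are likely to depend on the written rule.

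**Working it through.** The plan gives no figure to reproduce here, so the check sets the passages side by side.

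**Conflict 1: irinotecan after confirmed ILD (triplet arm)**

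1. A patient develops a trigger event. Under the Table 8.2.3.2 row all drugs are held, irinotecan included.
2. Non-infectious ILD is confirmed. The row stops oxaliplatin and is silent on irinotecan, 5-FU and leucovorin.
3. Two readings follow.
   - *The row governs.* ILD was not excluded, so the hold has no release. Irinotecan is neither resumed nor discontinued.
   - *The Section 8.2.3 bullet governs.* Oxaliplatin has been discontinued, so 5-FU, leucovorin and irinotecan continue.
4. General rules that might decide between them:
   - Section 8.2 lets other components continue if the investigator attributes the toxicity solely to one component. This is permissive and does not say how ILD is to be attributed.
   - Section 8.2 ends consolidation chemotherapy when a hold for a treatment-related event reaches 30 days. It acts only if the hold lasts that long.
   - Footnote c of Table 8.2.3.2 stops the regimen if toxicity is unresolved after 4 weeks (28 days), but also says to resume at grade 1 or less. It is attached to the main part of the table; the continued part with the respiratory row has its own footnotes.
   - Section 12.2 allows stopping for unacceptable adverse events or on the investigator's judgment, patient by patient.

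   If the symptoms of confirmed ILD settle to grade 1 within 28 days, neither time limit is reached and both readings remain open.

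**Conflict 2: threshold and scope of the hold (both arms)**

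| | Tables 8.2.1.3 and 8.2.3.2 | Section 10.2, nursing guidelines |
|---|---|---|
| Dyspnea, hypoxia, pneumonitis/infiltrates, fibrosis | hold from grade 2 | hold from grade 3 |
| Cough | hold from grade 3 | hold from grade 3 |
| Drugs held | all therapy | oxaliplatin |

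The thresholds differ for four of the five terms in Section 8.2. The scope differs throughout.

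**Size**

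- Planned irinotecan (Table 7.2.3): 150 mg/m2 x 8 cycles = 1200 mg/m2.
- Section 10.6 prints its cumulative doses in mg/m; I assume mg/m2. In cycles at full dose: 400/150 = 2.7, 750/150 = 5.0, 1000/150 = 6.7. These doses are therefore reached at cycle 3 (450), cycle 5 (750) and cycle 7 (1050), all within planned treatment.
- Expected cases: 1% x 380 = 3.8. A rate below 1% means fewer than 4 triplet patients, if the Section 10.6 rate carries over to this regimen.

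**The case against.** The strongest reply is that the row is specific and the bullet general, so the row should prevail. On that reading irinotecan stays held, and the 30-day rule in Section 8.2 would in time end chemotherapy. A reader might infer from the row and the bullet together that the protocol directs sites to restart irinotecan in confirmed ILD. The documents do not support that as a plain statement: it needs the bullet to override the row's own hold. A reader might also infer that irinotecan has no rule at all for ILD. That is wrong, since the hold on all therapy covers it. What stands is that the bullet is worded as mandatory and has no ILD exception, and that Section 8.2.3 does not say which instruction prevails.

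On the hold trigger, Section 10.2 is a nursing bullet in the drug-information section. It does not tell staff to treat at grade 2, it requires a chest x-ray and an oxygenation assessment for shortness of breath, and applying the Section 8.2 hold would breach nothing in it. That is fair, and cough agrees in both places. But a hold limited to grade 3 or higher states a different threshold, and a hold of oxaliplatin alone a different scope.

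It is also true that ILD is listed as rare, and that the cumulative-dose arithmetic shows only that the range is reachable. Section 10.6 gives no incidence at those doses, and it does not say from which dose its onset interval is counted.

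**Conclusion.** The protocol contradicts itself in two places. In the mFOLFIRINOX arm, the Table 8.2.3.2 row and the Section 8.2.3 bullet give no single answer on irinotecan after confirmed ILD. In both arms, Section 8.2 and Section 10.2 differ on the scope of the hold, and on its grade threshold for four of five respiratory terms. The general stopping rules may end treatment in individual patients but resolve neither conflict.

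Fewer than 4 of 380 triplet patients would be expected to have irinotecan-related ILD, on the assumption that the rate in Section 10.6 applies. The 380 triplet patients and the 760 in total are the numbers covered by the rules, not expected cases.

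Two further inferences should be resisted. The ILD instruction has the same wording in the mFOLFOX6 and mFOLFIRINOX tables, but that does not establish that it was carried over without thought for irinotecan. Nor do the documents show that the comparison of toxicity between arms (objective 2.2.4) would be distorted. The point is one of internal consistency in safety instructions; power, alpha and sample size do not depend on it.

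**What to change.** In the next amendment:

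- Reconcile the Section 8.2.3 bullet and the respiratory row of Table 8.2.3.2 with the irinotecan toxicities in Section 10.6, so that the mFOLFIRINOX instructions state one consistent status for irinotecan after confirmed ILD.
- Reconcile Tables 8.2.1.3 and 8.2.3.2 with the Section 10.2 nursing guidelines, so that grade threshold and scope of the hold are the same wherever they appear.

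The study team decides the clinical content; this review takes no position on which rule is right. The cost is protocol wording only, with no added tests, visits or patients.

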#### 8.2.4 Treatment Management of Patients on Chemoradiation\*

For management of capecitabine or 5-FU related toxicities, please see Table 8.2.2.2 ([Section 8.2.2](#)).

Table 8.2.4.1: Dose levels for capecitabine during chemoradiation

|              | Dose Level 0
Starting Dose
(mg/m  /d) | Dose Level -1
(mg/m  /d)         | Dose Level -2
(mg/m  /d)        | Dose Level -3
(mg/m  /d) |
|--------------|---------------------------------------------------------|-------------------------------------------------|------------------------------------------------|-----------------------------------------|
| Capecitabine | 1650 per day in two divided doses on days of RT         | 1240 per day in two divided doses on days of RT | 930 per day in two divided doses on days of RT | Discontinue                             |

Table 8.2.4.2: Dose levels for 5-FU during chemoradiation

|                                                                                                           | Dose Level 0
Starting Dose
(mg/m  ) a | Dose Level -1
(mg/m  ) a | Dose Level -2
(mg/m  ) a | Dose Level -3
(mg/m  ) |
|-----------------------------------------------------------------------------------------------------------|--------------------------------------------------------------------|----------------------------------------------------|----------------------------------------------------|---------------------------------------|
| Infusional 5-FU                                                                                           | 225 mg/m  iv continuous infusion                       | 170 mg/m  iv continuous infusion       | 125 mg/m  iv continuous infusion       | Discontinue                           |
| a: continuous infusion Monday-Friday on radiation days or 7 days per week based on preference of the site |                                                                    |                                                    |                                                    |                                       |

**\*NOTE: If in the opinion of the investigator, a toxicity is considered to be due solely to the radiation, then the radiation can be held at the investigator's discretion. The rationale for treatment break and the duration of the**

**break needs to be documented. Investigators are encouraged to reach out to [name] and/or [name] to discuss concerns with radiation toxicity resulting in a treatment break.**

### **8.2.5 Dose Modifications for Obese Patients**

There is no clearly documented adverse impact of treatment of obese patients when dosing is performed according to actual body weight. Therefore, all dosing is to be determined solely by actual weight without any modification unless explicitly described in the protocol. This will eliminate the risk of calculation error and the possible introduction of variability in dose administration. Failure to use actual body weight in the calculation of drug dosages will be considered a major protocol deviation. Physicians who are uncomfortable with calculating doses based on actual body weight should recognize that doing otherwise would be a protocol violation. Physicians may consult the published guidelines of the American Society of Clinical Oncology Appropriate Chemotherapy Dosing for Obese Adult Patients with Cancer: American Society of Clinical Oncology Clinical Practice Guideline. J Clin Oncol 30(13): 1553-1561, 2012.

## **9.0 ADVERSE EVENTS**

The prompt reporting of adverse events is the responsibility of each investigator engaged in clinical research, as required by Federal Regulations. Adverse events must be described and graded using the terminology and grading categories defined in the NCI's Common Terminology Criteria for Adverse Events (CTCAE), Version 5.0. The CTCAE is available at [ctep.cancer.gov/protocolDevelopment/electronic\\_applications/ctc.htm](http://ctep.cancer.gov/protocolDevelopment/electronic_applications/ctc.htm). Attribution to protocol treatment for each adverse event must be determined by the investigator and reported on the required forms. Please refer the NCI Guidelines: Adverse Event Reporting Requirements for further details on AE reporting procedures.

